##### 6.1.2.3. *Patient exit interviews*

Any qualitative data arising from the patient exit interviews will be typed into Word documents for export to NVivo qualitative data management software. All typed records will be checked for accuracy against the original questionnaires. Back-up files of word documents will be stored after each data entry session.

##### 6.1.2.4. *IDIs*

The IDIs will be administered using the appropriate topic guide by the interviewer. An assistant will take notes of the discussion. All interviews will also be recorded using a digital voice recorder. Summaries of the interviews will be written in the language of the interview, and will then be translated into English if necessary. Summaries of the interviews will be typed into Word documents for export to NVivo qualitative data management software. All typed records will be checked for

accuracy against the original recordings and field notes of the assistant. Back-up files of word documents will be stored after each data entry session.

#### *6.1.2.5. Semi-structured questionnaires*

Any qualitative data arising from the semi-structured questionnaires will be typed into Word documents for export to NVivo qualitative data management software. All typed records will be checked for accuracy against the original questionnaires. Back-up files of word documents will be stored after each data entry session.

#### *6.1.2.6. FGDs*

The FGDs will be facilitated by a moderator and the assistant will take notes of the discussion and non-verbal communication in English. All FGDs will also be recorded using a digital voice recorder. Recordings of the FGDs will be transcribed into the local language, and then translated into English. The transcripts will be checked for accuracy against the original recordings and field notes by members of the field team. The transcripts and discussion notes will be reviewed for themes and re-organized according to discussion topics. Back-up files of transcripts will be stored after each data entry session.

#### *6.1.2.7. Structured contextual record*

Qualitative data from the contextual record will be typed into Word documents for export to NVivo qualitative data management software. All typed records will be checked for accuracy against the original questionnaires. Back-up files of word documents will be stored after each data entry session.

## **6.2. QUALITY ASSURANCE AND QUALITY CONTROL**

All members of the study team will be trained in the project objectives, methods of effective communication with study participants, and collection of high quality data. Study team members will receive additional training specific to the tasks they will perform within the project including interviewing techniques and completing questionnaires. Standard Operating Procedures (SOPs) will be written for all project activities and booklets of all relevant documents will be provided to each member of the project team. Study group meetings will be conducted by the principal investigator to assess progress of the study, address any difficulties, and provide performance feedback to the members of the study group. Any corrections to data collection forms will be made by striking through the incorrect entry with a single line and entering the correct information adjacent to it, according to Good Clinical Practice guidelines [45]. The correction will be initialled and dated by the investigator. The investigators will allow all requested monitoring visits, audits or reviews.

## **6.3. RECORDS AND STORAGE**

All study documents will be kept in secured filing cabinets in the Infectious Disease Research Collaboration offices. The principal investigator will be responsible for the security of all project documents. Back-up files of databases will be stored onto the main project server after each data entry session. Participants will be identified by their study ID number, and participant names will not be entered into the computerised database.

#### **6.4. DATA SHARING**

This project is one of 16 participating in the ACT Consortium ([www.actconsortium.org/](http://www.actconsortium.org/)). As part of the ACT Consortium, a policy liaison network will be organized to help synthesize data from the multiple projects and communicate the results to policy makers. Consortium researchers will share data with the policy liaison network to facilitate analyses and ensure broad dissemination of the research findings.

## **7 ANALYTICAL PLAN**

---

### **7.1. QUANTITATIVE DATA**

Categorical variables from the self-filled questionnaires, patient exit interviews, semi-structured questionnaires, structured contextual record, and supply records, will be compared using the chi-square test or Fisher's exact test. Pairwise comparisons of continuous variables will be made using a two-sample t-test or non-parametric test when appropriate. A p-value < 0.05 (two-tailed) will be considered statistically significant. Analysis will be done using STATA (Stata, College Station, TX, USA).

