### **5.3.2. Health worker communication assessments + patient exit interviews**

We aim to conduct communication assessments with at least one health worker in each health facility in both the HFI and standard care arms (10 in each arm). Each communication assessment will consist of at least three, and no more than five, health worker/caregiver interaction records. The communication assessments will be conducted immediately before and up to 6 weeks after the HFI training in patient-centered services, and then approximately six months following the training for a total of three cycles. The same health workers will be assessed at each time point to evaluate for changes over time. We will evaluate approximately 20-25 health workers chosen by convenience sampling. Therefore conducting up to 125 health worker/caregiver interactions in each time period; 375 in total, depending on the number of health workers and patients available at the health centers on the days of the study. One health worker will be chosen from each of the level II health centers, and 1-2 health workers will be chosen from each of the level III centers. Exit interviews will be conducted with all consenting caregivers who participated in the assessments, up to a maximum of 125 interviews at each time point, 375 in total.

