|                                                                                                                                                                                       | 2 = No                 | [ ] [ ]                |
| Overall, how satisfied were you with the consultation today?                                                                                                                   | 1 = Very satisfied     | 3 = Somewhat satisfied |
|                                                                                                                                                                                       | 2 = Satisfied          | 4 = Not satisfied      |
|                                                                                                                                                                                       |                        | [ ] [ ]                |
| Do you have any additional comments about this consultation with the health worker?                                                                                            |                        |                        |
|                                                                                                                                                                                       |                        |                        |

[figure not shown][figure not shown][figure not shown][figure not shown][figure not shown]

[ ] [ ] [ ] [ ] [ ]

IDI Study ID

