**SECTION 7: ATTITUDE TOWARD WORK (Self-filled)**

|                                                                                          |                                                 |                                                                            |
|------------------------------------------------------------------------------------------|-------------------------------------------------|----------------------------------------------------------------------------|
| 1. Overall I am very satisfied in my job.                                         | 1 = Strongly agree
2 = Agree
3 = Disagree | 4 = Strongly disagree
88 = Don't know
99 = Refused to answer [ ] [ ] |
| 2. I am most motivated to do my job as health worker by the salary I receive.     | 1 = Strongly agree
2 = Agree
3 = Disagree | 4 = Strongly disagree
88 = Don't know
99 = Refused to answer [ ] [ ] |
| 3. I am most motivated to do my job as health worker by my desire to help people. | 1 = Strongly agree
2 = Agree
3 = Disagree | 4 = Strongly disagree
88 = Don't know
99 = Refused to answer [ ] [ ] |
| 4. I am able to complete all of the work I am expected to do each day.            | 1 = Strongly agree
2 = Agree
3 = Disagree | 4 = Strongly disagree
88 = Don't know
99 = Refused to answer [ ] [ ] |
| 5. The health workers who get promoted are the ones that are best at their job.   | 1 = Strongly agree
2 = Agree
3 = Disagree | 4 = Strongly disagree
88 = Don't know
99 = Refused to answer [ ] [ ] |
| 6. The salary I receive is fair, given my level of training and experience.       | 1 = Strongly agree
2 = Agree
3 = Disagree | 4 = Strongly disagree
88 = Don't know
99 = Refused to answer [ ] [ ] |
| 7. This health center provides everything I need to do my job well.               | 1 = Strongly agree
2 = Agree
3 = Disagree | 4 = Strongly disagree
88 = Don't know
99 = Refused to answer [ ] [ ] |
| 8. The district management team communicates well with our health center          | 1 = Strongly agree
2 = Agree
3 = Disagree | 4 = Strongly disagree
88 = Don't know
99 = Refused to answer [ ] [ ] |

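### Section 7.1 would test the ordered satisfaction, confidence and attitude items without using their order; an ordinal method that respects health centre should be named

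*Supplement*

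**What the plan says.** Section 7.1 sets one rule for all categorical data: variables from the patient exit interviews, the semi-structured questionnaires, the "structured contextual record, and supply records, will be compared using the chi-square test or" Fisher's exact test. The only rank-based option comes in the next sentence: "Pairwise comparisons of continuous variables will be made using a two-sample t-test or non-parametric test when appropriate". The threshold is "A p-value < 0.05 (two-tailed) will be considered statistically significant". Sections 7.1 to 7.3 name no ordinal, trend or rank method for category data and no effect measure.

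The instruments hold ordered items.

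- Appendix O (exit interview) has 15 closed items. Ten are yes/no. Five are ordered: satisfaction with treatment, welcome, and "Overall, how satisfied were you with the consultation today" have 4 levels; confidence in recovery and how the worker made the caregiver feel have 3.
- Appendix U, Part 1 (both arms) has 18: four 3-level confidence items in Section 5, six 4-level agreement items in Section 6, and eight in Section 7, such as "Overall I am very satisfied in my job". All 18 also carry codes 88 (don't know) and 99 (refused).

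On numbers, section 5.3.2 states: "We will evaluate approximately 20-25 health workers chosen by convenience sampling". Exit interviews run "up to a maximum of 125 interviews at each time point, 375 in total". Section 5.7 plans up to 10 health-worker questionnaires per arm, with every facility represented.

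**The concern.** In a 2 x k table, Pearson chi-square and Fisher's exact test give the same result however the k columns are arranged. They look for any difference in distribution and spend k - 1 degrees of freedom on it. The intervention is meant to move caregivers and staff towards better ratings, and a shift along the scale can be captured with 1 degree of freedom. For that kind of effect the stated rule is less efficient than it need be.

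The result is also hard to use. A significant chi-square on a 4-level item does not say which arm did better or by how much, and section 5.5 gives the purpose of the exit interviews as finding the level of caregiver satisfaction. These are key measures of caregiver satisfaction and staff attitude in the evaluation.

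**Working it through.** **The plan's own counts.** 25 health workers x 5 interactions = 125 per cycle, and 125 x 3 cycles = 375. Both match section 5.3.2. An even split gives 62 v 63 per arm. The stated minimum is 20 x 3 = 60 per cycle, or 30 per arm. There is no power figure to reproduce.

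**Degrees of freedom alone.** Let a 1-df test have 80% power at two-sided 0.05. Its noncentrality is (1.960 + 0.842)^2 = 7.85. The same noncentrality referred to chi-square on k - 1 df gives:

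- 3 levels (2 df): 70.9%, a loss of 80 - 70.9 = 9.1 points
- 4 levels (3 df): 64.5%, a loss of 80 - 64.5 = 15.5 points
- 2 levels (1 df): no loss

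**At the plan's sample sizes.** Simulation with 20,000 replicates: Pearson chi-square against the tie-corrected Wilcoxon rank-sum test, between arms within one cycle, independent responses, a common odds ratio (OR). The ranges run over four assumed response distributions for 4 levels and three for 3 levels.

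| n per arm | Levels | OR | Chi-square power | Rank power | Loss (points) |
|---|---|---|---|---|---|
| 62 v 63 | 4 | 2 | 32-40% | 49-57% | 17 |
| 62 v 63 | 4 | 2.5 | 53-65% | 72-81% | 16-18 |
| 62 v 63 | 4 | 4 | 88-95% | 96-99% | 3-8 |
| 62 v 63 | 3 | 2 | 34-44% | 44-55% | 10 |
| 62 v 63 | 3 | 2.5 | 54-68% | 65-78% | 10-11 |
| 30 v 30 | 4 | 2 | 15-20% | 27-31% | 11-12 |
| 30 v 30 | 4 | 2.5 | 25-33% | 41-50% | 16-17 |
| 30 v 30 | 3 | 2 | 17-23% | 24-30% | 7 |
| 10 v 10 | 4 | 2 | 6-8% | 11-13% | 5-6 |
| 10 v 10 | 4 | 4 | 15-22% | 28-37% | 13-16 |

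So at the minimum sample the loss is smaller at OR 2, but about the same as at the maximum sample at OR 2.5.

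**Clustering of exit interviews.** Interviews come 3 to 5 per health worker, within centres randomised as clusters. Take 10 v 10 centres, 6 interviews each (60 per arm, close to 62), 4 levels and an assumed intracluster correlation (ICC); the documents give none.

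| ICC | Type I error: chi-square / rank, both unclustered | Power at OR 2: unclustered chi-square | Power at OR 2: centre means |
|---|---|---|---|
| 0.05 | 6.9% / 8.4% | 35-37% | 38-41% |
| 0.10 | 8.5% / 10.8% | 35-37% | 32-33% |
| 0.20 | 12.7% / 15.7% | 34% | 22% |

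The rank-test error varies a little between simulations: about 7 to 8% at ICC 0.05 and 10 to 11% at 0.10. Part of the unclustered rank test's apparent power is therefore false positives, and unclustered chi-square is not a valid benchmark either. When both kinds of test are adjusted for centre, the ordered one stays ahead under a one-directional shift, but the margin is narrower than with independent data and shrinks as the ICC rises.

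**Questionnaire.** With at most 10 per arm and every one of the 10 facilities represented, there is one respondent per centre. Nothing is nested within centre here.

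**The case against.** Four points on the other side have force.

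1. **The loss is not general.** A reader might infer that the plan loses some 15 points of power on these items. The documents do not support a flat figure: they give no effect size, distribution or ICC, and the table shows losses from about 3 to 18 points at 62 v 63 depending on levels and effect. This stands.
2. **Chi-square can win.** For one assumed non-monotone 4-level difference it has 75% power against 18% for the rank test. This is true, but the intended effect is directional, so it does not justify an unordered test as the only one.
3. **The larger defect is ignored clustering.** At ICC 0.10 and above, a valid centre-level test has less power than the invalid unclustered chi-square. A reader might infer that swapping in a rank test restores the lost power; the second table shows that it does not do so validly. This limits the claimed gain, but not the case for using the order.
4. **Section 7.1 is silent on ordinal items**, so an analyst could treat scale scores as continuous and use the non-parametric clause. That is possible but unstated, and it leaves the choice of test open until the data are seen.

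The setting also matters. This is an explanatory, largely qualitative evaluation, and the trial's primary outcomes sit in ACT PRIME. A reader might take the exit items as the main measure of patient-centred care. Sections 5.5 and 7.2 give that role for communication to the scored audio recordings (MPCC). The training questionnaires go only to intervention-arm trainees and trainers, so no between-arm contrast is lost there.

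**Conclusion.** The point holds in a limited form. As written, 5 exit-interview items and 18 questionnaire items would be tested without their order. At about 62 per arm, with independent responses and a proportional shift of OR 2 to 2.5, that costs about 16 to 18 points of power for 4-level items and about 10 for 3-level items. It costs little at large effects and nothing on yes/no items. For the 10 v 10 questionnaire both tests have low power at moderate effects, so the choice of test matters less there than reporting an estimate with its interval.

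These figures assume an even split, a between-arm comparison within one cycle, and response distributions that the documents do not supply. Once centre clustering is respected, the full gap is not recovered. What the change buys is a valid, directional estimate, more efficient than an unordered test given the same cluster adjustment.

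**What to change.** Add to section 7.1:

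- **Ordered items:** use an ordinal method that accounts for health centre. Either proportional-odds regression with a centre random effect or a small-sample-corrected robust variance, or centre-level mean scores compared across the 10 v 10 centres. Report the common odds ratio or mean difference with a 95% confidence interval.
- **Health-worker questionnaire:** with one respondent per centre, a centre random effect can be neither estimated nor needed; the same ordinal comparison without it is enough.
- **Codes 88 and 99:** treat as off-scale and report their counts by arm.
- **Nominal and yes/no items:** keep chi-square or Fisher, with allowance for clustering where responses are nested in centres.

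Cost: a sentence or two, no new data, and Stata, already named, can do it. The price is an assumption: proportional odds for the model, or equal spacing of levels for mean scores. Showing the full distribution by arm beside the estimate would reveal a non-monotone difference that the ordered test could miss.

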## 1.2. THE ACT PRIME STUDY

In the ACT PRIME study, enhanced health facility care will be compared to the current standard of care provided by lower level government-run health facilities, supplemented by services provided through the private sector and community-based interventions, using a cluster-randomized design. There will be 20 health centers randomized to each study arm: 10 health centers in the health facility intervention arm and 10 health centers in the standard care arm. ACT PRIME began in December 2010, and the intervention will be rolled-out in March 2011. The objectives and outcomes of ACT PRIME are provided in Table 1.1 below.

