## 5.3. STUDY POPULATION

Within the seven sub-counties of the study area, there are 22 lower-level government run health facilities, including 17 level II health centers, and 5 level III health centers; 20 will be included in ACT PRIME. These 20 health centers will be randomly allocated to the health facility intervention arm or the standard care arm for a total of 10 health facilities in each arm. Clusters to be included in ACT PRIME are defined as the catchment areas of the health centers including households that are located within a 2 km radius of the facilities. Only households located within the clusters will be included in the sampling frame for ACT PRIME. ACT PROCESS follows the same sampling frame as ACT PRIME; participants for each type of data collection methodology are defined below.

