### **7.2. AUDIO RECORDINGS**

The health worker communication assessment audio recordings will be analyzed at the individual assessment level using the MPCC which has been validated and shows interrater reliabilities (interclass correlations) of 0.80-0.83. The coding is based on three components of patient-centered communication and produces a score for each component. These scores will be used to measure health worker responsiveness to patient concerns and produce a mean score of patient-centered communication ranging from 0 (not patient-centered) to 1 (very patient-centered) [44]. The audio recordings will be coded by trained social scientists, each coding one half of the assessments. All of the assessments will be dual-coded and compared for accuracy. Descriptive statistical analysis on MPCC scores will be done using STATA (Stata, College Station, TX, USA).

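### Section 7.1 tests the patient exit interviews with methods for independent records, without allowing for the 20 randomised health centres or the repeatedly assessed health workers

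*Supplement*

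**What the plan says.** The trial being evaluated is set up "using a cluster-randomized design" (section 1.2). Section 5.3 states: "These 20 health centers will be randomly allocated to the health facility intervention arm or the standard care arm", ten to each.

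Communication assessments and exit interviews take place in both arms (sections 5.3.2 and 5.5). About 20 to 25 health workers are chosen. Each is recorded with three to five caregivers per cycle, and consenting caregivers are interviewed on leaving. There are three cycles: before the training, up to six weeks after it, and about six months after it. Section 5.3.2 adds: "The same health workers will be assessed at each time point to evaluate for changes over time". The ceiling is 125 interviews per time point and 375 in total.

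Section 7.1 lists the exit interviews among its data sources. Categorical variables "will be compared using the chi-square test or Fisher's exact test. Pairwise comparisons of continuous variables will be made using a two-sample t-test", with a non-parametric test as the alternative. The threshold is stated: "A p-value < 0.05 (two-tailed) will be considered statistically significant". The section names neither the unit of analysis nor the contrasts to be tested. No other section supplies a method for clustered or repeated data.

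Section 7.2 deals with the audio recordings separately. They "will be analyzed at the individual assessment level using the MPCC", and the statistical analysis of those scores is descriptive.

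**The concern.** Chi-square, Fisher's exact, two-sample t and rank tests all assume independent records. Caregivers who see the same health worker in the same centre share that worker's manner, the staffing and the drug stock. Their answers will tend to be alike. Because whole centres were allocated to arms, this shared variation falls entirely on the arm comparison, and a record-level test leaves it out of the standard error.

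The consequence is that chance differences between a few workers or centres could be reported as effects of the intervention on caregiver satisfaction. For change over time the tests have a different fault: they treat the rounds as separate samples although the same workers return. The study exists to explain why the intervention did or did not work, so a spurious or a missed process effect would feed straight into that explanation.

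**Working it through.** **The plan's own figures.** 25 workers x 5 caregivers = 125 per round; x 3 rounds = 375. Both agree with section 5.3.2. These are logistic ceilings; no power, effect size or intracluster correlation (ICC) is given. The floor follows from one worker per centre and three caregivers each: 20 x 3 = 60 per round. It falls further if some caregivers decline the interview.

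**Arm comparison, by formula.** With m records per centre, the variance of a record-level comparison is understated by the factor DE = 1 + (m - 1) x ICC. The actual two-sided error of a nominal 5% test is 2 x [1 - Φ(1.96/√DE)]. The ICC is assumed and is on the observed scale.

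| Assumed ICC | Ceiling, m = 125/20 = 6.25: DE | Ceiling: actual error | Floor, m = 3: DE | Floor: actual error |
|---|---|---|---|---|
| 0.05 | 1.26 | 8.1% | 1.10 | 6.2% |
| 0.10 | 1.53 | 11.3% | 1.20 | 7.4% |
| 0.20 | 2.05 | 17.1% | 1.40 | 9.8% |
| 0.30 | 2.58 | 22.2% | 1.60 | 12.1% |

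**Arm comparison, by simulation.** Nearly all outcomes on the exit interview form (Appendix O) are yes/no or have three or four ordered categories, so the chi-square test is the one that matters. The simulated item had 70% prevalence (assumed) and an ICC of 0.05 to 0.40 set on an underlying normal scale. The same ICC on that scale gives a smaller correlation between the yes/no answers, so these errors are lower than the formula's at equal ICC.

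- Ceiling, 125 interviews per round: uncorrected chi-square error about 7% to 20%.
- Floor, 60 interviews: about 5.5% to 10.5%. A separate run put the upper end at 12.2%.
- t-test on 10 v 10 centre values: close to 5% throughout.

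**Before/after comparison.** Take K workers with m interviews each per round. Let the total variance be 1, the worker share be ICC, and a fraction f of that worker share be specific to the cycle.

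- True variance of the difference between rounds: (2/K) x [f x ICC + (1 - ICC)/m].
- Variance assumed by the unpaired test: about 2/(K x m).
- Ratio, true over assumed: 1 - ICC + m x f x ICC.

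The ratio exceeds 1 when f > 1/m. With five interviews per worker, the unpaired test turns liberal once more than one fifth of the worker variance is cycle-specific; with three, once more than one third is.

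Simulated two-sample t-test, 10 workers, m = 5:

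| Assumed ICC | Worker effects stable (f = 0) | Half cycle-specific (f = 0.5) | Wholly cycle-specific (f = 1) |
|---|---|---|---|
| 0.10 | 4.0% | 6.6% | 10.1% |
| 0.30 | 2.4% | 11.1% | 19.0% |

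A paired t-test on worker means gave 4.8% to 5.3% throughout. These runs used a continuous outcome. The direction carries over to yes/no items; the exact sizes need not.

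**The case against.** Several points on the other side are fair.

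- **The unit is not stated.** Section 7.1 does not say that individual interviews are the unit, and no separate analysis plan is shown, where such detail is often placed. This stands as a limit: the record-level reading is an inference. It is still the natural one, because chapter 7 is the analytical plan, it names its tests, and it mentions no centre summary.
- **The inflation may be small.** At the floor, with a low ICC, the excess is slight. A continuity-corrected chi-square there gave 3.2%, 3.6% and 7.8% at ICC 0.05, 0.10 and 0.40. This stands as the lower end of the range. It does not make the test valid, because the correction offsets the clustering only by accident.
- **The study is explanatory.** It has no primary endpoint or powered hypothesis, and the effectiveness outcomes belong to ACT PRIME. This limits what is at stake. But section 7.1 sets a significance threshold, so the error rate matters for what it reports.

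A reader might also infer more than the documents support.

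- **Patient-centred communication scores.** One might say that their p-values are wrong too. Section 7.1 does not list the recordings and section 7.2 only describes the scores, so no test of them is planned.
- **Self-filled questionnaires and supply records.** These come from the intervention arm only and give no arm contrast. No section plans to test one training topic against another.
- **Larger error rates.** Pooling rounds, or applying a t-test to a continuous interview score, would give bigger figures. No section plans to pool, and the form defines no such score.
- **Main arm contrast.** The documents do not give the exit interviews that status; Table 4.1 places them under process evaluation.

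**Conclusion.** The point holds for the patient exit interviews. Section 7.1 applies independence-based tests to data nested in 20 randomised centres and repeated within workers, and nothing in the protocol accounts for either.

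Under the record-level reading, arm comparisons are too liberal: about 7% to 20% actual error at 125 interviews per round and about 5.5% to 10.5% at 60, against a nominal 5%. This rests on an assumed 70% prevalence, an assumed latent-scale ICC of 0.05 to 0.40, and an uncorrected chi-square test.

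Unpaired before/after tests are invalid without a fixed direction. They are conservative if worker effects are stable and liberal if these vary enough between cycles. It would be wrong to say simply that they miss real change.

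The health-worker semi-structured questionnaires are not affected in the same way. Section 5.7 plans up to ten per arm with at least one per facility, which is about one record per centre.

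**What to change.** In section 7.1:

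1. Name the health centre as the unit for arm comparisons of the exit interviews. Either calculate one proportion or mean per centre per round and compare 10 v 10 (t-test on 20 - 2 = 18 degrees of freedom, or a permutation test), or fit a mixed model with centre and health-worker effects and small-sample degrees of freedom.
2. For change over time, use paired comparisons of worker-level summaries or a mixed model with worker effects. Caregivers are recruited afresh in each cycle, so pairing is possible only at worker level.
3. Say that simple two-sample tests are kept for the health-worker semi-structured questionnaires.
4. In section 7.2, add that any arm or time comparison of the communication scores, if one is made, will use the same clustered methods.

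No new data are needed: Appendix O already records health centre and health worker. The cost is a little more analysis and less favourable arm p-values. At the ceiling, 125 interviews per round carry the information of 125/DE independent ones, about 99, 82, 61 and 49 at observed-scale ICC 0.05, 0.10, 0.20 and 0.30. As an illustration with assumed rates of 60% v 80% and 62.5 interviews per arm, power would be 69% if records were independent, and about 59%, 51%, 40% and 33% at those ICCs. That loss comes from the design; the present wording only hides it.
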